## Abstract

This randomized controlled trial aims to evaluate the efficacy of a cognitive training program using video games in improving neuropsychological, neurological, immunological, and inflammatory parameters in childhood cancer survivors. This study will recruit 56 patients aged 8–17 years who have completed cancer treatment 1–8 years prior to enrollment. Participants will be randomized to either the video game intervention or waiting group. The primary objectives are analyzing potential changes in neuropsychological tests covering all neurocognitive domains, neuroimaging tests (structural, diffusion, and functional imaging), and immune and inflammatory biomarker levels after video game intervention. The secondary objectives are to define the prevalence of neurocognitive deficits in the study population, analyze psychological and emotional self-perception and parental perception after the intervention, and assess the feasibility of implementing this new intervention methodology. The inclusion criteria comprise specific diagnoses (central nervous system [CNS] cancer, hematologic malignancies, extracranial solid tumors, and nonmalignant hematological diseases requiring allogeneic hematopoietic progenitor transplantation) and treatments (CNS surgery, radiotherapy, intrathecal/intraventricular chemotherapy, neurotoxic systemic chemotherapy, and hematopoietic stem cell transplantation). Patients with active disease, relapse, or prior neurological or psychiatric pathology will be excluded. This study will improve the understanding and management of neurocognitive sequelae in childhood cancer survivors and ultimately enhance their quality of life. Trial identifier: NCT06312969

## 1 Introduction

Childhood cancer is the leading cause of death from the disease in children in developed countries. Fortunately, advances in research have allowed better diagnosis and treatment in recent years, improving survival at 5 years to over 80% and to over 90% in some of the most frequent neoplasms, such as acute lymphoblastic leukemia (ALL) [1].

This rise in survival means that there is an increasing number of survivors of childhood cancer, reaching a prevalence between 450 and 1240 childhood cancer survivors per million people in Europe in the last 30 years [2]. This situation requires healthcare professionals and researchers to focus their attention not only on curing the disease but also on improving the quality of life of survivors.

Both the disease itself and the treatment administered can produce medium- and long-term sequelae that appear in more than half of the patients. Neurocognitive effects are among the most frequent and important. According to several studies, between 17 and 75% of cancer survivors present with this condition in variable grades between six months and 20 years after the end of treatment [3]. The most frequently affected areas are memory, learning, concentration, reasoning, executive functions, attention, and vision-spatial abilities [4]. This is a major problem affecting the quality of life of childhood cancer survivors and has been frequently neglected until now, with no established diagnostic and therapeutic strategies in pediatric hemato-oncology units.

In addition to neurocognitive involvement, there are some structural and functional changes in the central nervous system (CNS) that have been reported by neuroimaging in childhood cancer survivors. These changes have been observed even in children with tumors outside the CNS and those with normal neurocognitive capacity [5]. The most frequent structural alteration is the reduction in gray matter volume and changes in the integrity of white matter in different locations, especially in the frontal lobe [6–8]. Functional alterations are studied using functional magnetic resonance imaging (fMRI). Some studies have attempted to identify the brain areas underlying the neurocognitive effects of chemotherapy, proposing hypoactivation in the parietal and prefrontal areas as the leading cause [9]. These studies have been infrequent to date, especially in children, and have less clinical correlation.

Video games have been used for years as a training tool for executive functions in different pediatric pathologies such as attention-deficit/hyperactivity disorder (ADHD) [10,11]. Their potential is so important that in the United States the Food and Drug Administration (FDA) has approved a video game as a prescription to reduce the severity of ADHD in pediatric patients [12]. Other studies have demonstrated structural and functional changes in healthy people using neuroimaging techniques after the use of video games, with an increase in the activation of certain brain areas [13,14].

Although growing evidence supports the presence of neurocognitive sequelae in survivors of pediatric cancer, there is considerable variability in the type and severity of deficits reported across studies, as well as in their estimated prevalence. Furthermore, the relationship between cognitive impairments and neurostructural or neurofunctional alterations remains unclear. Despite the increasing recognition of these late effects, there is no established routine for the systematic screening of neurocognitive sequelae in survivorship care, nor are there widely accepted, engaging, and effective cognitive training interventions tailored to this population. This study aims to address these gaps by proposing a multifaceted, game-based intervention and by exploring cognitive, neuroimaging, and immunological outcomes in an integrated manner.

## 2 Methods and analysis

### Study design

This project is a single-center, open-label, parallel group, two-armed randomized clinical trial evaluating changes in neurological, neuropsychological, immunological, and inflammatory parameters after a cognitive training program with video games compared to a waiting group without the program (Fig 1).

**Fig 1 pone.0314118.g001:**
[figure not shown]
Study algorithm. Participants were divided into two age groups (8–12 and 13–17 years) and underwent baseline assessment (T0) at the time of recruitment. They were then randomized to either the intervention group or the waitlist control group. A second assessment (T + 3) was conducted 12 weeks later, followed by a third assessment (T + 6) 12 weeks later. After this period, the participants in the waitlist group were offered the opportunity to receive the intervention over the following 12 weeks. STG = Skill Training Game.

### Study objectives

#### 2.1.1 Primary objectives.

The primary objective of this trial is to demonstrate relevant changes in neurocognitive, neurological, immunological, and inflammatory evaluations after a training program with videogames. The primary endpoints are defined as follows:

Clinically relevant improvement from moderate effect sizes in the following parameters measured by neuropsychological tests: Symbol Digit Modalities Test (SDMT), Continuous Performance Test, third edition (CPT 3), Spain-Complutense Verbal Learning Test for Children (TAVECI)/Spain-Complutense Verbal Learning Test (TAVEC), Vocabulary subtest of the Wechsler Intelligence Scale for Children, fifth edition (WISC-V)/ Weschler Intelligence Scale for adults, fourth edition (WAIS-IV) Vocabulary and Digit Span subtests, verbal fluency tests, STROOP, Rey-Osterrieth Complex Figure (ROCF), Test Of Non-verbal Intelligence, fourth edition (TONI-4) (forms A and B), and the Behavior Rating Inventory of Executive Function, second edition (BRIEF-2) questionnaire.Statistically significant changes in neuroimaging tests. The following variables will be measured:Structural imaging: volume measurement and Voxel Based MorphometryDiffusion Imaging: diffusion maps and structural connectivityFunctional imaging: resting state and task based fMRIStatistically significant changes in immune and inflammatory biomarker levels before and after treatment:Study of lymphocyte populations by parametric flow cytometry: T lymphocytes, B lymphocytes, natural killer (NK) lymphocytes, NK T lymphocytesStudy of inflammatory cytokines by LUMINEX: interleukin (IL) -2, IL-4, IL-6, Tumor necrosis factor (TNF) alpha, interferon (IFN) gamma, IL-10, IL-17TH, IL-1R antagonist

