### Variables and instruments

The variables measured in this project, the instruments used and the informants who will complete each measure are detailed below:

Sociodemographic (sex, age, educational level) and clinical variables (weight and height, blood pressure, heart rate, physical examination, and neurological examination). This data will be collected with an initial survey created *ad hoc* for the present study.Ecological Executive Functioning. The BRIEF-2 questionnaire [15] will be used. This questionnaire will be completed by the patient’s parents or legal guardians.Emotional and behavioral problems. The BASC-3 [16] will be administered, including both parent-reported and self-reported versions. This questionnaire assesses the personal and interpersonal/social domains of each patient, covering areas such as adaptive skills, resiliency, externalizing and internalizing problems, school problems, and relationships with parents and peers.Cognitive processing speed. The SDMT [17] will be administered to patients, in its oral form, to assess their processing speed of information.Visual sustained attention/vigilance. The CPT 3 [18], will be administered to the patients. This test computes several scores, as follows: Detectability, Omissions, Commissions, Perseverations, Hit Reaction Time (HRT), HRT Standard Deviation, Variability, HRT Block Change and HRT Inter-Stimulus Interval Change.Immediate and delayed verbal memory. A Spanish test based on the California Verbal Learning Test will be used. Specifically, the TAVECI [19] will be administered to patients aged 8–16 years, and the TAVEC version [20] will be applied to patients aged 16–18 years. This test allows for the calculation of a wide range of scores, and in this study, the following scores will be used: Immediate Recall, Short Delay Free Recall, Short Delay Cued Recall, Long Delay Free Recall, Long Delay Cued Recall, Long Delay Recognition, Semantic clustering strategies, Serial clustering strategies, False positives, and Discriminability.Semantic memory. The WISC-V [21] will be administered to patients up to the age of 16.11 years, and the adult version, fourth edition (WAIS-IV) [22], will be administered to patients up to 18 years of age.Verbal working memory and cognitive flexibility. The Digit Span subtest of the WISC-V [21] or WAIS-IV version [22] will be used. Three neurocognitive domain-specific scores will be considered (Forward, Backward, and Sequencing subscales), as well as the global score (Digit Span), as a measure of cognitive flexibility [21].Verbal fluency. The Verbal Fluency Test (TFV) [23] will be administered to patients, calculating the following eight scores: Phonological fluency, Semantic fluency, Excluded-letter fluency, Total Fluency Index, Errors in phonological fluency, Errors in semantic fluency, Errors in excluded-letter fluency and Total errors.Cognitive interference inhibition. The STROOP test [24] will be applied to patients and the following four scores will be computed: the Word reading, the Color naming, the Color-word and Resistance to Interference.Visuo-constructive organizational ability and immediate and delayed visual memory. The Rey Complex Figure Test (RCFT) [25] will be applied to patients, generating the following four scores: a copy score (accuracy regarding visual–spatial constructional ability), time required to copy the figure, and two delayed recall scores (at 3 and 30 min).Non-verbal Intelligence. Both forms (A and B) of the TONI-4 [26] will be administered to the patients.Structural image: volume of white matter, gray matter, total intracranial volume, volume of cerebral lobes, and different subcortical structures. Voxel-based morphometry (VBM).Diffusion Imaging: diffusion maps (fractional anisotropy, mean diffusivity, etc.) and structural integrity.Functional imaging: Task-based fMRI: functional differences related to a working memory task; Resting State fMRI: analysis of functional connectivity (Seed Based Analysis and Independent Component Analysis).Study of lymphocyte populations by parametric flow cytometry: T lymphocytes, B lymphocytes, NK lymphocytes, and NK T lymphocytes.Study of inflammatory cytokines: IL-2, IL-4, IL-6, TNF alpha, IFN gamma, IL-10, IL-17a, IL-1R antagonist.

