### Statistical methods

The data will be processed primarily using the statistical software IBM SPSS Statistics 30.0, among others, and the following analyses will be performed:

Initially, descriptive analyses will be performed on all the variables to detect any potential errors or outliers in the dataset. Zero-order correlation analyses will then be computed to determine the strength of association between the variables, and partial correlation analyses will be conducted to assess the association while excluding the influence of confounding variables.

The main statistical analysis will consist of a mixed Analysis of Covariance (ANCOVA) to evaluate between-group effects (intervention vs. waiting list), within-group effects over time (T0, T + 3, and T + 6), and their interactions, controlling for relevant covariates. These covariates will include age, sex, baseline cognitive performance, cancer diagnosis, and treatment modality (e.g., CNS radiation, neurotoxic chemotherapy). *P*-value adjustments will be performed for multiple comparisons. Assumptions of normality, homogeneity of variances, and sphericity will be examined and addressed as needed. Additional analyses will include latent growth models to examine cognitive trajectories, and multiple linear regression models to determine the relative contribution of predictor variables on outcome measures, as previously described [27].

The diagnostic group (CNS vs. non-CNS tumors) will be included as a covariate in the main analyses, and exploratory subgroup comparisons between CNS and non-CNS survivors will be conducted to assess the potential differences in cognitive, neuroimaging, and biomarker outcomes.

All statistical analyses will be complemented with appropriate effect size indices for each statistical test (e.g., *f*, omega square, and *R*^*2*^ indices) [28]. Additionally, the Reliable Change Index (RCI) will be computed to determine the real change in each individual score between measurements over time [29].

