The original power analysis was performed using GPower 3.1.9.4, assuming a repeated-measures ANCOVA (2 × 3 design) with a statistical power of 0.95, α = 0.05, and a moderate effect size (f = 0.25), resulting in a minimum required sample size of 36 participants. However, because GPower does not account for intra-subject correlation (ICC), this estimation corresponds to a fixed-effects model. As the analysis will use a mixed model with repeated measures, we acknowledge that the ICC could affect power. To increase transparency, we have considered ICC values between 0.3 and 0.6, which suggest that between 42 and 48 participants may be needed to maintain the same level of power. This is feasible within our recruitment plan.

Missing data will be handled using multiple imputation under the missing-at-random (MAR) assumption. Sensitivity analyses will compare the imputed results with complete-case analyses, and other techniques, such as pattern-mixture models, may be used if appropriate.Randomization will be performed automatically using the REDCap platform and stratified by age group. Once a patient has been assigned, the study investigators will inform them and their families via telephone calls.

Investigators responsible for the clinical follow-up will not be blinded. However, those conducting neuropsychological and neuroimaging assessments will be blinded to group allocation to minimize bias in the outcome evaluation.

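### Twenty-two named items plus all imaging measures are primary with no lead endpoint or success rule, and the stated 0.95 power is for one unnamed test at α = 0.05 although p-value adjustment is promised

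*Protocol article*

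**What the plan says.** Section 2.1.1 (Primary objectives) opens with "The primary objective of this trial is to demonstrate relevant changes in neurocognitive, neurological, immunological, and inflammatory evaluations after a training program with videogames" and then defines three groups of primary endpoints.

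- **Neuropsychological:** "Clinically relevant improvement from moderate effect sizes in the following parameters measured by neuropsychological tests", followed by ten instruments: SDMT, CPT 3, TAVECI/TAVEC, Vocabulary, Digit Span, verbal fluency, STROOP, Rey figure, TONI-4 and BRIEF-2.
- **Imaging:** "Statistically significant changes in neuroimaging tests", covering volumes, voxel-based morphometry, diffusion maps, structural connectivity, and resting-state and task fMRI.
- **Biomarkers:** statistically significant change in four lymphocyte populations and eight cytokines.

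Variables and instruments lists the scores that each instrument yields. For CPT 3 these are "Detectability, Omissions, Commissions, Perseverations, Hit Reaction Time (HRT), HRT Standard Deviation, Variability, HRT Block Change and HRT Inter-Stimulus Interval Change"; for verbal fluency the text has "calculating the following eight scores".

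Statistical methods says of p-values that "adjustments will be performed for multiple comparisons". The power paragraph in the same section describes a single 2 × 3 repeated-measures ANCOVA "with a statistical power of 0.95, α = 0.05, and a moderate effect size" (f = 0.25). It gives a minimum of 36, then 42 to 48 after considering ICC values of 0.3 to 0.6. Planned enrolment is 56. The endpoint that was powered is not named.

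**The concern.** The set of primary endpoints, the promise to adjust and the power basis are all stated, and they do not fit together. Section 2.1.1 ranks no endpoint first and sets no rule for success. The power paragraph treats the trial as one test at the full 0.05.

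The promised adjustment can be read in two ways. If it spans the primary endpoints, each is tested at a much smaller α than the one used for sizing, and 0.95 no longer describes any of them. If it covers only visit or pairwise contrasts within an endpoint, the chance of a false positive somewhere among the primaries is not held at 0.05. On either reading it is undefined what result would count as demonstrating the primary objective, and the choice could be made after the results are seen.

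**Working it through.** **1. Counting the primaries.** Section 2.1.1 alone gives 10 instruments + 4 lymphocyte populations + 8 cytokines = 22, plus imaging.

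With the scores in Variables and instruments, the neuropsychological count is SDMT 1 + CPT 3 9 + TAVECI/TAVEC 10 + Vocabulary 1 + Digit Span 4 + fluency 8 + STROOP 4 + Rey figure 4 + TONI-4 1 + BRIEF-2 1 = 43. BRIEF-2 is taken as one because no number is given, and the two TONI-4 forms are counted once. Then 43 + 12 = 55, plus imaging.

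**2. The plan's own figure.** Method: noncentral F test for group by time, with k = 2 groups, m = 3 visits and sphericity assumed.
- λ = f²·N·m/(1−ρ), df1 = (k−1)(m−1) = 2, df2 = (N−k)(m−1).
- For f = 0.25, α = 0.05 and power 0.95, the required N is 60 at ρ = 0.3, 44 at ρ = 0.5 and 36 at ρ = 0.6.

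The stated 36 therefore appears only with ρ = 0.6, which the article does not give for that figure. This is a separate matter, and the point here does not depend on it.

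**3. Power at N = 56.** λ = 0.0625 × 56 × 3/(1−ρ) = 10.5/(1−ρ), which is 15.0, 21.0 and 26.25 at ρ = 0.3, 0.5 and 0.6; df2 = 54 × 2 = 108. Data are taken as complete, since no dropout rate is stated. Bonferroni is my illustrative choice, since the article names no method.

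| Tests | α per test | ρ = 0.3 | ρ = 0.5 | ρ = 0.6 | N for 0.95 (ρ = 0.3 / 0.5 / 0.6) |
|---|---|---|---|---|---|
| 1 | 0.05 | 0.938 | 0.987 | 0.997 | 60 / 44 / 36 |
| 22 | 0.05/22 = 0.00227 | 0.661 | 0.863 | 0.946 | 98 / 72 / 58 |
| 55 | 0.05/55 = 0.00091 | 0.556 | 0.793 | 0.909 | 108 / 78 / 64 |

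At N = 56, reaching 0.95 per endpoint needs ρ of about 0.61 for 22 tests and 0.65 for 55. Both lie above the article's range of 0.3 to 0.6. Imaging would add further tests.

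**4. Error rate if the adjustment does not span the primaries.** Each test is taken at 0.05.
- 12 biomarkers, independent: 1 − 0.95^12 = 0.46.
- 22 tests, independent: 1 − 0.95^22 = 0.68.
- 55 tests, independent: 1 − 0.95^55 = 0.94.
- 55 tests, simulated with equal pairwise correlation: about 0.83, 0.64 and 0.42 at correlations 0.3, 0.5 and 0.7.

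The 22 and 55 figures apply a significance rule to the neuropsychological scores, which section 2.1.1 does not do. The 12-biomarker figure stays within a group that is judged by significance.

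**The case against.** **Adjustment is promised, and its method belongs in the SAP.** This stands. A reader might infer that the trial has no multiplicity control, or a 94% false-positive rate. The article supports neither. The 0.94 needs independence, no adjustment across endpoints and a 0.05 rule everywhere, whereas many of these scores overlap (the global Digit Span sits beside its own subscales). The missing method is not the finding. The finding is that the primary set and the power basis, both stated here, conflict.

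**The neuropsychological criterion is a moderate effect size, not p < 0.05.** This also stands, and it limits the error-rate figures. It does not supply a success rule, because nothing says on how many of the ten instruments the effect must appear.

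**Fifty-five is an inference.** Correct: section 2.1.1 names 22 items plus imaging, and treating every score as its own primary is plausible but not stated. With 22 tests, power per endpoint is still below 0.95 over the article's whole correlation range, though only just at 0.6.

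**Bonferroni is strict, and the loss is per endpoint.** True. A less strict method would lose less. If any one success sufficed and two independent endpoints truly had f = 0.25, the chance of at least one success at ρ = 0.5 with 55 tests would be 1 − (1 − 0.793)² = 0.957. A fixed sequence would also preserve α and power for its first test. So it would be wrong to say that power fails under every possible rule. But the article states no such rule, and its sample size reflects none.

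**Conclusion.** The point holds in this form: the article names many primary endpoints without a lead or a success rule, promises p-value adjustment, and sizes the trial as if there were one unadjusted test.

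If the adjustment spans the primaries, power per endpoint at N = 56 is 0.66 to 0.946 for 22 tests and 0.56 to 0.91 for 55, against the stated 0.95. This assumes Bonferroni, f = 0.25, correlation 0.3 to 0.6, complete data, sphericity and the group-by-time test. If the adjustment stays within endpoints, the trial-wide error rate is uncontrolled: for 55 tests at 0.05 it is 0.94 under independence and about 0.4 to 0.8 at pairwise correlations of 0.7 to 0.3, with the caveat that the neuropsychological criterion is an effect size.

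This should be settled before analysis by arm, because until then the confirmatory question is undefined.

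**What to change.** Before data are analysed by arm, by documented amendment with a registry update:

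1. Name one primary outcome at one visit, tested at two-sided 0.05. It can be a single performance-test score chosen by the investigators or one prespecified composite of standardised scores.
2. Make the remaining neuropsychological, imaging and biomarker measures secondary or exploratory, with false-discovery-rate control within each domain.
3. Restate the power at N = 56 for that single test, with its correlation assumption.

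No new patients or assessments are needed. The costs are that imaging and biomarkers lose the primary label and that the restated power may fall below 0.95. The single-test row in the working does not carry over, because it is for an interaction across three visits and not for a comparison at one visit.
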